# Using a Tailored Digital Health Intervention for Family Communication and Cascade Genetic Testing in Swiss and Korean Families With Hereditary Breast and Ovarian Cancer: Protocol for the DIALOGUE Study

**DOI:** 10.2196/26264

**Published:** 2021-06-11

**Keywords:** HBOC, proportion of informed at-risk relatives, coping, communicating, decisional conflict, cultural and linguistic adaptation, implementation, RE-AIM, mobile phone

## Abstract

**Background:**

In hereditary breast and ovarian cancer (HBOC), family communication of genetic test results is essential for cascade genetic screening, that is, identifying and testing blood relatives of known mutation carriers to determine whether they also carry the pathogenic variant, and to propose preventive and clinical management options. However, up to 50% of blood relatives are unaware of relevant genetic information, suggesting that potential benefits of genetic testing are not communicated effectively within family networks. Technology can facilitate communication and genetic education within HBOC families.

**Objective:**

The aims of this study are to develop the K-CASCADE (Korean–Cancer Predisposition Cascade Genetic Testing) cohort in Korea by expanding an infrastructure developed by the CASCADE (Cancer Predisposition Cascade Genetic Testing) Consortium in Switzerland; develop a digital health intervention to support the communication of cancer predisposition for Swiss and Korean HBOC families, based on linguistic and cultural adaptation of the Family Gene Toolkit; evaluate its efficacy on primary (family communication of genetic results and cascade testing) and secondary (psychological distress, genetic literacy, active coping, and decision making) outcomes; and explore its translatability using the reach, effectiveness, adoption, implementation, and maintenance framework.

**Methods:**

The digital health intervention will be available in French, German, Italian, Korean, and English and can be accessed via the web, mobile phone, or tablet (ie, device-agnostic). K-CASCADE cohort of Korean HBOC mutation carriers and relatives will be based on the CASCADE infrastructure. Narrative data collected through individual interviews or mini focus groups from 20 to 24 HBOC family members per linguistic region and 6-10 health care providers involved in genetic services will identify the local cultures and context, and inform the content of the tailored messages. The efficacy of the digital health intervention against a comparison website will be assessed in a randomized trial with 104 HBOC mutation carriers (52 in each study arm). The translatability of the digital health intervention will be assessed using survey data collected from HBOC families and health care providers.

**Results:**

Funding was received in October 2019. It is projected that data collection will be completed by January 2023 and results will be published in fall 2023.

**Conclusions:**

This study addresses the continuum of translational research, from developing an international research infrastructure and adapting an existing digital health intervention to testing its efficacy in a randomized controlled trial and exploring its translatability using an established framework. Adapting existing interventions, rather than developing new ones, takes advantage of previous valid experiences without duplicating efforts. Culturally sensitive web-based interventions that enhance family communication and understanding of genetic cancer risk are timely. This collaboration creates a research infrastructure between Switzerland and Korea that can be scaled up to cover other hereditary cancer syndromes.

**Trial Registration:**

ClinicalTrials.gov NCT04214210; https://clinicaltrials.gov/ct2/show/NCT04214210 and CRiS KCT0005643; https://cris.nih.go.kr/cris/

**International Registered Report Identifier (IRRID):**

PRR1-10.2196/26264

## Introduction

### Background

In 2018, there were approximately 2.1 million breast cancer diagnoses and more than 600,000 associated deaths worldwide [1,2]. The worldwide average breast cancer incidence is 74.2 per 100,000 women [3], with approximately 25% of cases occurring in women younger than 50 years and in women with a family history of cancer [4,5]. Approximately 5%-10% of breast cancer and 20% of ovarian cancer cases occur due to germline pathogenic variants associated with hereditary breast and ovarian cancer (HBOC) syndrome, most commonly observed in the *BRCA-1* and *BRCA-2* genes (hereafter *BRCA*). The prevalence of germline pathogenic variants differs among ethnic groups [6]; however, Switzerland and Korea have a similar prevalence ranging from 23% to 26% [7,8].

The availability of genetic services (counseling and testing) for actionable hereditary cancer syndromes such as HBOC enables population-level cancer prevention [9]. Blood relatives of HBOC cases have a 12.5%-50% probability of inheriting the same pathogenic variant and can be tested with 100% accuracy. Chemoprevention, prophylactic surgery, and intensive surveillance can lower cancer risks for relatives who test positive, whereas those who test negative are excluded from these interventions [10-12]. The Centers for Disease Control and Prevention Office for Public Health Genomics recommend genetic testing in cancer-free individuals with a known HBOC family history and in patients with cancer who have strong indications of HBOC syndrome (eg, ovarian cancer) [13]. Cascade genetic screening is a systematic effort to identify and test all blood relatives of HBOC cases to determine whether they also carry the same pathogenic variant [10]. The CASCADE (Cancer Predisposition Cascade Genetic Testing) Consortium in Switzerland promotes cascade genetic screening for HBOC [14,15], whereas the Korean Hereditary Breast Cancer (KOHBRA) network identifies the prevalence of HBOC-associated pathogenic variants in the Korean population [16,17].

Despite calls to action for HBOC cascade genetic testing, there are systemic barriers to its implementation. Privacy laws worldwide, including Switzerland and Korea, restrict health care providers from revealing genetic information to anyone except the tested individual, who has the right not to disclose this information, despite implications for relatives’ health [18-20]. The potential benefits of genetic testing are not being effectively communicated through family networks, leading to more than 50% of at-risk individuals not using genetic services and not receiving important information from a credible source [21-23]. Second-degree and male relatives, those living further away, and those with an estranged relationship with the mutation carrier are most likely not to be informed about genetic testing [24,25]. Despite these difficulties, a family-based approach in communicating hereditary cancer risk is advantageous because it may reach relatives through the social bonds and functions already existing within the family network, and it is not limited to those in contact with the health care system [26].

Interventions that support mutation carriers during the disclosure of genetic test results can reduce psychological distress and provide relatives with accurate and credible information about cascade genetic testing. Technology-enabled education is not inferior to face-to-face genetic consultations [27,28], but it increases access to services and cost-effectiveness [29-32]. The Family Gene Toolkit [33] is a web-based intervention designed to increase prerequisites for HBOC cascade testing, that is, active coping, open family communication, and informed decision making. The prototype Family Gene Toolkit was tested in the United States for acceptability and patient satisfaction with excellent results, confirming its value for these families. However, it is not available in other linguistic and cultural contexts. Adapting existing interventions, rather than developing new ones, takes advantage of the previous valid experiences without duplicating efforts.

In summary, HBOC cascade genetic testing, meaning the identification and testing of blood relatives, provides risk management options for those with a germline pathogenic variant and excludes confirmed noncarriers (ie, negative testing when there is a known pathogenic variant in the family) from intensive surveillance and risk-reducing measures. Due to privacy laws, mutation carriers have the sole responsibility to inform blood relatives about genetic test results and advocate for genetic services. Digital health platforms can support mutation carriers during the disclosure process and provide relatives with accurate and credible information.

### Objectives

The DIALOGUE study will build a bilateral research infrastructure to support collaboration and multidisciplinary initiatives around HBOC in Switzerland and Korea. The specific aims are to develop the K-CASCADE (Korean–Cancer Predisposition Cascade Genetic Testing) cohort in Korea by expanding an existing research infrastructure developed by the CASCADE Consortium in Switzerland; develop a digital health intervention to support open communication and cascade genetic testing in HBOC families, based on the linguistic and cultural adaptation of the Family Gene Toolkit; evaluate the efficacy of the digital health intervention on primary (communication of genetic test results to relatives and cascade genetic testing) and secondary (psychological distress, genetic literacy, coping, and decision making) outcomes; and explore the translatability of the platform using the reach, effectiveness, adoption, implementation, and maintenance (RE-AIM) framework.

## Methods

### Design

The DIALOGUE study will use a cohort design to establish the K-CASCADE in Korea and a randomized controlled trial (RCT) design to test the effects of digital health intervention in the Swiss and Korean contexts. The study will measure clinical and process outcomes in real-world conditions, including different settings, participants, and resources [34,35].

#### Aim 1: Develop the K-CASCADE Cohort

The K-CASCADE cohort will identify and survey mutation carriers and blood relatives as its archetype, the Swiss CASCADE cohort, using similar design, assessments, and procedures for sample identification and data collection [14]. Adult Korean men and women with *BRCA* pathogenic variants will be invited to the K-CASCADE cohort. They will also be asked to invite their first- and second-degree relatives and their first cousins for cascade genetic screening. Similar to the Swiss CASCADE, it is envisioned that the K-CASCADE cohort will include known mutation carriers, untested relatives with unknown mutation status, and relatives who tested negative for the pathogenic variant.

#### Aim 2: Adapt the Digital Health Intervention

The content of the Family Gene Toolkit is driven by theory [36] and supported by empirical findings [37-41]. It is designed to address challenges related to the quantity and complexity of genetic information mutation carriers are asked to communicate with family members [42,43]. Understanding HBOC (eg, probability of mutation, prognosis, prevention, and treatment) and the accuracy of genetic testing are important for decision making. Inherited cancer risk requires ongoing management and, thus, active coping with health challenges. Mutation carriers’ personal values and communication skills are important for the disclosure of genetic cancer risk. The Family Gene Toolkit embraced the above challenges and included 4 modules designed to increase knowledge of cancer genetics (module 1), provide decisional support for genetic testing to untested relatives (module 2), increase active coping with common challenges faced by HBOC families (module 3), and provide skills-building communication training (module 4; Figure 1). The adapted Family Gene Toolkit will include the 4 original modules and a fifth module about the management of cancer risk based on recommendations from the National Comprehensive Cancer Network [44].

**Figure 1 figure1:**
[figure not shown]
Examples from the Family Gene Toolkit.

The research team will create tailored messages based on the linguistic and cultural adaptations of the modules. Tailoring is a process that *fits* the message to meet one’s personal needs and characteristics, rather than targeting group criteria [45,46]. Tailored messages improve whether and how one listens to a message and its impact on behavior change. Shallow tailoring involves elements of appearance (eg, female or male mutation carriers), whereas deep tailoring involves more complex elements of relevance (eg, coping style). Adaptation of the Family Gene Toolkit involves elements of both shallow and deep tailoring based on preintervention assessments of participants’ characteristics such as sex, affected with cancer versus cancer-free, and tendency to rely more on a specific coping style. The research team will use readily available e-learning products with different tailored messages, multiple interactions and assessments, and a device-agnostic interface for the adaptation of the Family Gene Toolkit. Messages will be developed in English and translated at the eighth-grade reading level while considering Swiss and Korean legislation, health insurance policy, cultural values, and national languages. Swiss and Korean stakeholders will review the content of the adapted Family Gene Toolkit and identify the required modifications by providing feedback on word choices, sensitivity of messages, and appearance. Mini focus groups and individual interviews with clinicians involved in genetic consultations will evaluate the prototype of each module and the tailoring elements. Focus groups with Swiss and Korean HBOC mutation carriers and relatives will provide suggestions to enhance the comprehensibility, usefulness, acceptability, and feasibility of the intervention. Feedback from clinicians and HBOC families will help in further refining each module and the tailored messages.

Assessing the usability of the adapted Family Gene Toolkit involves task-oriented assignments about the most important functions and features of the website as well as the ease and user-friendliness of navigation. Participants will *think aloud* while navigating each module and complete each task [47]. They will also evaluate the tailored messages for readability and comprehension.

Swiss and Korean participants will complete the 5 modules at their own pace, but within a timeframe of 4 weeks after they first engage with the platform. The 4-week interval enables information assimilation and adequate time to reflect and act based on tailored messages while providing a controlled learning environment. Feedback will be based on baseline responses, including tailored advice about improvements that can be made.

Consistent with testing real-world alternatives [48], the DIALOGUE study will provide a comparison website with targeted (generic) information. The comparison website will mimic the structure and functions of an existing website [49]. The adapted Family Gene Toolkit and the comparison website will be technically implemented in the same system that will collect baseline and follow-up data, randomize participants, deliver the intervention and the comparison website, track access and use of the platform, and provide a user-friendly experience to participants.

#### Aim 3: Evaluate Intervention Efficacy on Primary and Secondary Outcomes

A cluster RCT will evaluate the magnitude of intervention effects as compared with the comparison website. Randomization will occur at the family level, that is, after baseline data collection, the digital health intervention will randomly assign mutation carriers to either intervention arm, stratifying for country. Invited relatives will be automatically directed to the same arm as the mutation carrier. All study participants will complete a survey at baseline (T_1_) before the intervention and again at 2 months (T_2_) and 6 months (T_3_) after the intervention. The 2- and 6-month follow-up time points will assess the short-term and long-term effects in line with our previous studies [33,50].

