### Recruitment and Procedures

#### K-CASCADE Cohort

The opportunity to participate in the K-CASCADE cohort will be advertised through the KOHBRA network, the Ovarian Cancer and Genetics study group, and other clinical sites. Recruitment procedures for Korean probands and relatives will follow steps and procedures similar to those outlined for the Swiss CASCADE cohort [14]. In short, index cases (first person in the family with the pathogenic variant) identified in participating centers will be invited to participate in the study by collaborating clinicians and through patient advertisements posted in the clinics. Potential participants will also be able to view information on the study website. Individuals carrying a *BRCA* pathogenic variant, and if they have at least one eligible relative based on pedigree data, will meet study recruiters to ask questions and provide written consent. To alleviate ethical concerns associated with contacting blood relatives without their explicit consent, the K-CASCADE cohort will approach them through probands, targeting only relatives the proband is willing to contact. This recruitment method is used by the Swiss CASCADE cohort and in previous family-based studies with very good recruitment outcomes [39,54]. Relatives agreeing to participate will also provide written consent. In the consent form, probands and relatives will indicate their willingness to invite additional relatives to the K-CASCADE, be contacted once a year for 5 years and provide updated information about their health, participate in a focus group or individual interview for the adaptation of the Family Gene Toolkit in Korean, and participate in an RCT for testing the effects of the adapted Family Gene Toolkit. Probands and relatives may participate in all or some of the study steps previously described.

Probands and relatives will provide baseline assessments via a URL link to the digital health intervention and a unique passcode. A second prompt will be sent 2 weeks later. If there is no response to the second contact, study recruiters will contact the participants by phone. Relatives will also provide written consent, and they will receive a URL with a unique passcode. The Swiss CASCADE platform will facilitate data collection in both countries to maintain the consistency and accuracy of data entry, data management, and analyses. Korean respondents will log on as K-CASCADE participants to provide survey data.

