#### Intervention Efficacy

After they complete the baseline questionnaires (T_1_), probands (index case) in both countries who agree to participate in an RCT and test the effects of the adapted Family Gene Toolkit will be emailed a unique URL link and passcode allowing them access to the digital health intervention. Furthermore, they will be able to log in and review the intervention modules multiple times using the same URL link and passcode. The system will randomize participants in a 1:1 ratio to either the digital health intervention or the comparison website. Stratification by country (Switzerland vs Korea) will be facilitated with different URL links for participants from each country. Participants will receive weekly email or text alerts, encouraging them to visit the website and complete viewing of the contents of the digital health intervention within 4 weeks. They will also receive email or text alerts to complete a knowledge quiz, an exercise for value clarification related to genetic testing, and a family communication rubric that will be included in the content of the different modules. Participants randomized to the comparison website will receive 1 email alert 2 weeks after they engage with the website. Relatives will be allocated to the same study arm as the respective proband and will also receive a URL link and a unique passcode. Relatives will first be asked to complete a consent form and then to complete the baseline survey, after which they will have access to either the adapted Family Gene Toolkit or the comparison.

Primary and secondary outcomes will be assessed at 2 months (T_2_) and 6 months (T_3_) after the intervention. We selected the 2- and 6-month follow-up time points to measure the short-term and long-term intervention effects, in line with our previous studies [33,50]. To minimize the attrition rate, if a response has not been received within 2 weeks from the time participants receive the URL link to the follow-up survey, then the study personnel will make 3 attempts to contact them by email or phone and encourage them to complete the survey.

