#### Intervention Translatability

Textbox 2 outlines RE-AIM outcomes to be assessed, which will help in evaluating the potential for a broader implementation and dissemination of the digital health intervention.

Reach, effectiveness, adoption, implementation, and maintenance outcomes assessed in the study.Reach (individual)Response rate of mutation carriers and relativesNumber of probands and relatives accessing the websiteDemographic, linguistic characteristics, and regionResponse rate to K-CASCADE (Korean–Cancer Predisposition Cascade Genetic Testing)Effectiveness (individual)Assess the number of times participants accessed each moduleAssess the number of relative invites initiated through the websiteEvaluate the acceptability, interest, usefulness, level of detail, relevance, and satisfaction follow-up surveyAdoption (setting, staff, and organization)Number of clinicians and new settings willing to participate in the studyDiversity (geographic, linguistic, etc) in participating settingsImplementation (setting, staff, and organization)Monitor referrals of mutation carriers from different clinical sitesEvaluate the cost for adapting modules for other hereditary cancer syndromes (eg, Lynch syndrome)Maintenance (individual and setting)Assess resources needed to maintain the websiteAssess the number of visits per month per year

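### Arm comparisons on outcomes measured in relatives, one of them listed as primary, are not protected by randomisation, because relatives enter on the invitation of a proband who is already randomised

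*Protocol article*

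**What the plan says.** Aim 3 of the protocol article sets the order: "Randomization will occur at the family level, that is, after baseline data collection, the digital health intervention will randomly assign mutation carriers". Relatives follow: "Invited relatives will be automatically directed to the same arm as the mutation carrier". The trial procedures (Recruitment and Procedures, Intervention Efficacy) repeat that "Relatives will be allocated to the same study arm as the respective proband" and add that "Relatives will first be asked to complete a consent form and then to complete the baseline survey", after which they can open the site of that arm.

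Inviting and informing relatives is also what the intervention is meant to change. One module is there to "provide skills-building communication training" (Aim 2). Among the RE-AIM effectiveness measures, Textbox 2 counts "the number of relative invites initiated through the" website.

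Table 2 lists three primary outcomes. One is measured only in relatives: a single 7-point item on untested relatives' intention to be tested, taken at baseline and follow-up. Decisional conflict in untested individuals is a secondary outcome. The analysis section plans a Wilcoxon-Mann-Whitney test on the proportion of informed relatives and descriptive statistics for the other primary and secondary outcomes.

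**The concern.** Randomising families makes the probands comparable. It makes relatives comparable only if who enters as a relative does not depend on the arm. Here entry passes through an invitation by the proband, made under the influence of the allocated website. The Background says who is usually left out: "Second-degree and male relatives, those living further away" and those estranged from the carrier. If the intervention succeeds, its arm should enrol more relatives, and relatives of a different kind.

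Success on the proband outcome would then make the relatives less comparable. A difference in testing intention or decisional conflict could reflect who was reached and not what the website did for them. The baseline raises a related issue. Aim 3 calls T1 a survey taken before the intervention, but for a relative enrolled by the trial procedure it precedes only that relative's own access to the site. It may come after the proband has used the modules and spoken to the relative.

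**Working it through.** The plan gives no figure for relative-level comparisons. Its sample size (104 evaluable probands, 52 per arm) concerns the proportion informed and does not bear on this point. The check is first structural, then an illustration of size.

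**Sequence for a family**

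1. The proband completes T1.
2. The proband is randomised and given access.
3. The proband invites relatives, at least partly through the website.
4. Invited relatives take the proband's arm, consent, complete T1 and get access.

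The article describes no step that fixes the set of relatives between 1 and 2.

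**Inputs for the illustration**

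- From the article: 52 probands per arm; 4 relatives invited per proband and a 50% response (K-CASCADE Cohort sample size section); up to 50% of relatives unaware (Abstract), used as a 50% control rate; a 25% increase in the proportion informed as the target effect.
- Assumed: the increase is absolute (50% to 75%); the 4 relatives are the pool from which the informed share is drawn; the most open relatives are reached first; the intervention has no true effect on relatives; the correlation ρ between being reached and the outcome score is 0.1 to 0.5; the within-family correlation is 0.1.

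**Relatives enrolled**

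- Control: 52 × 4 × 0.50 × 0.50 = 52
- Intervention: 52 × 4 × 0.75 × 0.50 = 78

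**Spurious difference.** Let openness be standard normal. If the top fraction q is reached, the mean openness of those reached is φ(z)/q, where z cuts off the upper fraction q.

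- q = 0.50: 0.798
- q = 0.75: 0.424
- Difference, intervention minus control: 0.424 - 0.798 = -0.374

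The expected difference in the score is -0.374 × ρ SD. If the 25% is read as a relative increase (50% to 62.5%), the multiplier is 0.607 - 0.798 = -0.191.

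| ρ | 50% vs 75% | 50% vs 62.5% |
|---|---|---|
| 0.1 | -0.04 SD | -0.02 SD |
| 0.3 | -0.11 SD | -0.06 SD |
| 0.5 | -0.19 SD | -0.10 SD |

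**If such a contrast were tested.** In 3000 simulated trials at 50% vs 75%, with family means compared by a two-sided 5% t test and no true effect, the rejection rate was 5.6% at ρ = 0, 5.6% at 0.1, 8.5% at 0.3 and 17% at 0.5. The simulation error around 5% is √(0.05 × 0.95/3000) = 0.4 points, so the first two are close to nominal.

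**Counting unenrolled relatives as failures.** This may look like a safe family-level alternative. With 52 × 4 = 208 listed relatives per arm and the same true share s intending to test, the counted share is 52s/208 = 0.25s in control and 78s/208 = 0.375s in intervention. The ratio is 1.5 in favour of the intervention with no effect on intention.

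**The case against.** The strongest reply is that the one formal arm comparison is little affected. The trial is sized on probands, the Wilcoxon-Mann-Whitney test concerns the proportion informed, and probands are randomised after their own baseline. Everything else is descriptive. This stands, and it rules out reading the point as a bias in the trial's main test. Descriptive status does limit false-positive claims, but it does not make the arms' relatives comparable, and one of these outcomes is labelled primary.

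Other inferences a reader might draw are not supported:

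- **The denominator is restricted to relatives the proband will approach.** The phrase "targeting only relatives the proband is willing to contact" is a recruitment rule of the K-CASCADE cohort, not a definition of the outcome. The article does not state the denominator. Table 2 also ticks the proportion informed at baseline, so some count of relatives must exist at that time.
- **Every relative's T1 is contaminated.** The article does not say when invitations fall relative to module use, and some relatives may already have consented and given a baseline through the cohort. The trial procedure does not limit relatives to these, so the risk remains but is not universal.
- **Adjustment for T1 will remove part of the effect.** No adjustment or change score is specified.
- **All the psychological and knowledge outcomes are affected.** Distress and genetic literacy are measured in probands too, and the proband contrasts on them remain randomised.

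**Conclusion.** The point holds for between-arm contrasts on outcomes measured in relatives, chiefly testing intention in untested relatives (listed as primary) and decisional conflict in untested individuals. They carry post-randomisation selection and cannot support a randomised claim. This follows from the order of events in the article and needs no numerical assumption.

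The size and direction cannot be known from the documents. The figure of about -0.04 to -0.19 SD rests on an assumed 50% versus 75% informed, the most open relatives being reached first, and ρ between 0.1 and 0.5. A smaller gain in reach gives less, and a negative correlation reverses the sign.

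It would go too far to conclude that the trial's main result is compromised. The proportion of informed relatives, compared between probands, remains a randomised comparison provided its denominator is fixed before allocation.

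**What to change.** - At proband T1, before randomisation, record all eligible first- and second-degree relatives and first cousins, from the pedigree data already used to check eligibility. Use this list as the fixed denominator of the proportion informed. It should not become a mandatory invitation list, since the cohort procedure leaves the choice of whom to approach with the proband.
- Move relatives' testing intention out of the primary outcomes, and label all relative-level arm contrasts as non-randomised and exploratory.
- Report the numbers of relatives listed, invited and enrolled, by arm and degree of relationship.
- Do not describe the T1 of relatives enrolled after allocation as pre-randomisation.
- If a family-level testing outcome is wanted, ascertain it for all listed relatives in the same way in both arms, for example by proband report, or give it with sensitivity bounds. Do not count unenrolled relatives as failures, because that favours the arm that enrols more.

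The cost is a slightly longer proband T1 survey, some changes of wording, and one fewer outcome labelled primary. An analysis plan can relabel the contrasts later, but it cannot recover a list that was not collected before randomisation.
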